### Ethical Considerations

The principal investigator will ensure this that study is conducted in full conformity with the current revision of the Declaration of Helsinki (last amended in October 2000, with additional footnotes added in 2002 and 2004). The principal investigator will ensure that this study is conducted in full conformity with relevant regulations and with the ICH Guidelines for Good Clinical Practice (CPMP/ICH/135/95) July 1996.  Our study was approved by the University of Otago Health Ethics committee (reference HD21/087).

Any important protocol modifications will be communicated in a timely manner to trial participants already enrolled and the DMC in a timely manner.

The results of this study will be disseminated through peer-reviewed publications and conference proceedings. Trial participants will be provided with the option to receive notification of any disseminated results upon enrollment.

## Results

As of February 2022, a total of 8 retrospective comparators have been recruited by email.

## Discussion

### Strengths and Limitations

This study is not a randomized trial and uses historical comparators, which may limit our ability to generalize the results due to confounding factors. We aim to mitigate the effects of potential confounding factors by matching comparators based on training experience. Potential confounding variables will be collected at baseline for both groups and explored for associations with our outcome measures. In monitoring the learning curves of both groups over time, a difference-in-difference analysis will be performed to explore simulator effects. The quality of patient data and logbook entries by historical trainees will determine the quality of our comparator data; however, we are confident that the primary outcomes we have chosen are sufficiently routinely collected for surgical cases.

This is the first surgical simulator validation study conducted across all New Zealand centers with early-stage trainees and will be invaluable for establishing a pathway for future New Zealand studies. In collaborating with the training organization at the early stages of testing, and continuous collaboration over the course of the project, the formal integration of this simulator into training can be streamlined. Collaborations for this study also exist with orthopedic surgeons in the United States. Successful multicenter testing in New Zealand is likely to lead to further testing in the United States, thereby improving the external validity of this simulator and possible integration into international training programs. 

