**Methods:**

This multicenter, interventional cohort study will involve orthopedic trainees from New Zealand in their first year of advanced training between 2019 and 2023. Advanced trainees with no simulator exposure who were in their first year in 2019-2021 will form the comparator cohort, while those in the years 2022-2023 will receive additional regular simulator training as the intervention cohort. The comparator cohort’s performance in pediatric SCHF surgery will be retrospectively audited using routinely collected operative outcomes and parameters over a 6-month period. Data on the performance of the intervention cohorts will be collected in the same way over a comparable period. The data collected for both groups will be used to determine whether additional training with an augmented reality training shows improved real-world surgical outcomes compared to traditional surgical training.

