### Recruitment

Intervention group trainees will be approached at training weekends to inform them about the study, to assess eligibility, and to receive consent. Comparator group trainees will be identified from the New Zealand Orthopaedic Association trainee registry and approached via email for this process. Enrollment for comparator group trainees will begin in February 2022, and enrollment for intervention group trainees will occur in the March training weekends of 2022 and 2023.

We aim to include data for 14 trainees in 2022; however, the number of trainees in 2023 is not yet known. The comparator cohort data will be retrospectively audited from trainees who undertook traditional training without exposure to the simulator during their 6 months of follow-up in the years 2019, 2020, and 2021 (n=41). We expect a total sample size of approximately 65 trainees, given an average of 12 new trainees per annum. The comparator group is matched based on their length of registered training at the start of follow-up, that is, first-year trainees with 2 months of registered training.

The in-theater performances of the comparator and intervention groups will be compared using cumulative sum charts for each of the primary outcomes to determine any differences in trends of skill acquisition according to the method of training. The simulator performance of the intervention group will be used to establish a learning curve and compared with in-theater learning curves.

Retrospectively matched trainees have been chosen instead of prospective randomized ones for the comparison group in order to maximize sample size and to avoid contamination. New Zealand only introduces 10-15 trainees per year into the orthopedic training program, and thus a prospective randomized trial will greatly limit the statistical power. There is also the chance of cross-group contamination as there is no way of ensuring comparator trainees located in the same area as intervention trainees will not use the simulator.

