#### Comparators

The comparator cohort’s follow-up will begin in February of each year. This is due to the change to the training schedule instated at the end of 2020 whereby trainees began their rotations in February instead of the prior December.

Primary outcomes will be collected retrospectively via trainee logbooks and patient PACS records for retrospective data. Secondary outcomes will not be collected for comparators.

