### Conclusions

The results of this pilot study will show the feasibility and efficacy of simulator use within New Zealand’s public health system. The long-term benefits to society will be both for the education of registrars and the health outcomes of patients. In particular, for trainees in localities with lower populations, this simulator can address the disparity in case volumes for those that would otherwise have been deprivileged by their location. Moreover, this simulator has been developed with minimizing costs and increasing accessibility as key objectives; it is cheaper than many currently available models and has low requirements for the environment. We envisage its frequent use as a valuable tool within hospital systems.

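### Simulator exposure coincides with calendar year, and neither matching on training length nor any planned comparison separates the two, so drift in either direction can bias the effect itself

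*Protocol article*

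**What the plan says.** The Abstract (Methods) assigns exposure by year: trainees "who were in their first year in 2019-2021 will form the comparator cohort, while those in the years 2022-2023 will receive additional regular simulator training". No year contains both kinds of trainee.

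Recruitment matches comparators on one variable, length of registered training at the start of follow-up, stated as 2 months. Strengths and Limitations presents this as the protection against confounding: "We aim to mitigate the effects of potential confounding factors by matching comparators based on training experience". The same paragraph says historical comparators may limit generalization, that potential confounders will be collected and explored, and that a difference-in-difference analysis of the learning curves will explore simulator effects.

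Statistical Analysis lists two-sample tests, cumulative sum curves (by individual and aggregated before versus after simulator training), and regressions on simulator uses, earlier and concurrent case counts, Gartland class and spatial scores. Calendar year is not among them.

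The Comparators section starts comparator follow-up in February of every year and explains: "This is due to the change to the training schedule instated at the end of 2020", when the rotation start moved from December to February. Study Design follows intervention trainees from May to November. The closing Conclusions section says: "The results of this pilot study will show the feasibility and efficacy of simulator use".

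**The concern.** The objective is whether adding the simulator improves in-theater performance. If theater time, imaging habits, supervision or case mix changed between 2019-2021 and 2022-2023 for any other reason, that change enters the cohort difference in full. Two trainees with equal months of training but different calendar years still differ in calendar year, so the matching cannot help. The number of simulator uses is zero in every comparator year, so as a regressor it carries the same confounding.

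This threatens internal validity: the estimate itself may be wrong. The article describes it as a limit on generalizing and then says the results will show efficacy. Drift toward better performance could create an apparent benefit, and drift the other way could hide a real one.

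**Working it through.** **Inputs from the article (Recruitment).** 41 comparators over 2019-2021; "We aim to include data for 14 trainees in 2022; however, the number of trainees in 2023 is not yet known"; "We expect a total sample size of approximately 65 trainees, given an average of 12 new trainees per annum".

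**Reproducing the stated total.** 41 + 2 × 12 = 65, which agrees. With the 14 planned for 2022, 41 + 14 + 12 = 67, which is also approximately 65.

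**Assumptions, not in the article.** Comparators split 14/14/13 by year and intervention trainees 12/12; one independent value per trainee with SD 1; two-sided 5% test; linear drift; no true simulator effect.

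**Calendar gap.** Comparator mean year = 2020 + (13 − 14)/41 = 2019.98. Intervention mean year = 2022.5. Gap = 2.52 years (2.49 with 67 trainees).

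**Spurious effect.** Bias = drift per year × 2.52. The standard error of the unadjusted difference is √(1/41 + 1/24) = 0.257 SD. The rejection rate is Φ(bias/0.257 − 1.96) + Φ(−bias/0.257 − 1.96).

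| Drift (SD/year) | Spurious effect (SD) | Rejections at nominal 5% |
|---|---|---|
| 0.05 | 0.13 | 8% |
| 0.1 | 0.25 | 17% |
| 0.2 | 0.50 | 50% |
| 0.3 | 0.76 | 84% |

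Simulated t tests (20,000 per setting) gave 16%, 47% and 82% for the last three rows.

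**Can the comparator years show the drift?** The sum of squared deviations of year among the 41 is 27 − 41 × 0.0244² = 26.98, so the slope has SE 1/√26.98 = 0.193 SD per year. Power to detect drift of 0.1, 0.2 or 0.3 SD per year is 8%, 18% and 34%. With only the 8 comparators recruited by February 2022 (3/3/2 assumed), power for 0.2 is 7%.

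**Would a linear year term cure it?** It would remove linear drift, but group and year correlate at 0.86 (variance inflation 3.9). The SE rises from 0.257 to 0.509 SD, and power for a 0.8 SD effect falls from 87.5% to 35%.

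**2021 comparators alone.** The remaining gap is 2022.5 − 2021 = 1.5 years, so drift of 0.1 to 0.3 SD per year still gives 0.15 to 0.45 SD. The SE is √(1/13 + 1/24) = 0.344 SD.

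**Months since rotation start when follow-up begins, on the stated dates:**

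| Cohort | Rotation start | Follow-up start | Months in |
|---|---|---|---|
| 2019, 2020 | December | February | about 2 |
| 2021 | February | February | about 0 |
| 2022, 2023 | February | May | about 3 |

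The stated match at 2 months therefore fits only the 2019 and 2020 comparators. The year trend mixes drift with a change in experience, and the 2021 contrast has the largest experience gap, in the direction that favors the simulator.

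**Difference-in-difference.** The simulator is first used in March and in-theater follow-up runs from May, so exposed trainees have no in-theater period before exposure. No unexposed trainees are observed in the same years.

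**The case against.** The article discloses that the study is not randomized and uses historical comparators. It calls itself a pilot and justifies the design by an intake of 10-15 trainees a year and the risk of contamination. All of that stands, and the design need not change.

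The difference-in-difference analysis is a real safeguard in part. Comparing change within follow-up would cancel a constant difference in level between cohorts. It would also cancel any simulator benefit already present when follow-up begins, and it would not remove drift in the rate of learning. It is exploratory and does not appear under Statistical Analysis.

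Year-by-year sensitivity analyses may sit in a document not shown, so their absence alone is no fault. What can be faulted is in the text: the matching offered against confounding, the description of bias as a generalizability issue, and the efficacy claim.

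A reader might infer that a time trend would simply be taken for a simulator benefit. The article does not support that: it gives no drift figure, and the one trend it describes, shorter work hours and fewer cases (Current Training), could plausibly work against later cohorts. The schedule change is documented only as a new start month; nothing shows that it altered supervision or performance.

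A reader might also infer that the three comparator years would expose any drift, or that 2021 gives a clean contrast. The slope's low power and the unequal starting points rule out both.

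**Conclusion.** The concern holds in this form: exposure and calendar year do not overlap, matching on training length leaves the gap of about 2.5 years intact, and no listed comparison or regression contains year. The bias can run either way and affects the estimate itself. Its size is unknown; a spurious effect of about 0.25 to 0.76 SD follows only if drift is 0.1 to 0.3 SD per year, under the assumptions listed. The planned difference-in-difference analysis reduces the problem for a constant shift but does not resolve it. The comparator data can inform the question only weakly, and a flat trend would not exclude drift. The result therefore supports a statement of association, not of efficacy.

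**What to change.** 1. Reconcile Study Design, Recruitment and Comparators on when follow-up starts, so that both cohorts are compared over the same months since rotation start.
2. On the aligned data, report each primary end point by comparator year (2019, 2020, 2021) with confidence intervals, and repeat the cohort comparison against 2021 comparators only. Label both as imprecise sensitivity analyses. Neither should decide whether efficacy may be claimed.
3. In Strengths and Limitations, state that calendar-time confounding can bias the effect in either direction. In Conclusions, describe the result as an association rather than as showing efficacy.

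The cost is two extra analyses with wide intervals and a softer conclusion. No new data are needed: the comparator audit is retrospective and draws on logbooks and records already in the plan.

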### Study Design

The intervention cohort is composed of trainees using the BoneDoc AR simulator at least once per month over a follow-up period of 6 months (May to November) in the years 2022-2023 (Figure 1).

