### Interventions and Comparators

#### Intervention

The simulator will be first administered at the March training weekends for each year. We will use these training weekends to test participants at baseline on the simulator and collect demographic data via survey. The simulator will be set up as one of the 15-minute assessment stations in the training weekend. Simulator sets will be distributed to individual trainees following the training weekend. Upon delivery of the simulator sets, the principal investigator will also provide aid to the trainee in identifying an appropriate environment for the simulator and address any setup issues.

It is then expected that trainees will undertake, at minimum, monthly 15-minute practices on the simulator for the next 6 months of training. These practice data are sent to a cloud server after each use. Note that the simulator training will be in addition to any routine training they will receive at their respective hospitals. Over this time, primary end points for each in-theater case will be taken over the course of follow-up through District Health Board (DHB) records, including patient picture archiving and communication system (PACS) records and trainees’ logbooks.

We will request intervention trainees to write out relevant patient data and end point results as the cases present to maximize accuracy. Trainees will be reminded monthly by email to provide case data and practice on the simulator. Their simulator performance will be assessed again in a controlled environment during the November training weekend. At this point, secondary end points will also be collected via survey.

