### Data Collection

#### Outcomes

##### Primary End Points—Collected for Each In-Theater Case Over Follow-up

Theater time and radiation time in seconds (radiation time may not be available from retrospectively assessed notes but will be attained where possible)—collected from procedure reports from electronic patient recordsNumber of fluoroscopy shots—collected from patient PACS recordsPin accuracy—accuracy is defined based on procedural recommendation literature—analyzed from patient PACS recordsComplication/nonideal union incidence—stratified for types of complications (nerve injury, vascular injury, loss of reduction, compartment syndrome, and infection)—collected from reviews of medical records and letters of referral from electronic patient notes

These primary end points have been determined as measurements of trainee performance, which are relatively easily retrieved from patient records and trainee logbooks.

The number of fluoroscopy shots and radiation time can be used to approximate the amount of radiation patients and staff are exposed to. In particular, for patients, theater time and radiation exposure have been shown to correlate to a higher chance of complications and thus should be avoided [21]. Studies have shown a decrease in both measurements for SCHF treatments with increased trainee proficiency [22,23]. Pin accuracy affects the stability of union, and there are well-established guidelines for ideal position of pins.

Ultimately, postoperative complications and nonideal union are the most crucial outcomes the trainees should aim to avoid. We do not expect to see high rates of these for either group, but overall rates will be monitored for comparison.

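### The planned difference-in-difference has no in-theater period before simulator exposure, so on the described windows it estimates late effect minus early effect, not the simulator effect

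*Protocol article*

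**What the plan says.** After conceding that historical comparators bring confounding, the protocol article (Discussion, Strengths and Limitations) states that, as the two groups' learning curves are followed, "a difference-in-difference analysis will be performed to explore simulator effects". It does not define the two periods of that contrast.

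The timing is given elsewhere:

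- **Exposure.** Under Intervention: "The simulator will be first administered at the March training weekends for each year". Sets go to individual trainees after that weekend, and practice at least monthly is expected for six months.
- **Follow-up.** Study Design describes simulator use "over a follow-up period of 6 months (May to November) in the years 2022-2023".
- **Outcome collection.** Under Intervention, "primary end points for each in-theater case will be taken over the course of follow-up"; the heading of the primary end points repeats this: "Collected for Each In-Theater Case Over Follow-up".
- **Baseline.** For intervention trainees the March baseline is a test on the simulator and a demographic survey. Strengths and Limitations adds that "Potential confounding variables will be collected at baseline for both groups". These are covariates, not operative outcomes.
- **Comparators.** They are different trainees, from 2019-2021, never exposed to the simulator (Recruitment).

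**The concern.** A difference-in-difference cancels a fixed gap between two groups because the earlier period is untouched by the intervention: whatever separates the groups then cannot be the intervention and can be subtracted. Here every in-theater case described for the intervention cohort comes after first exposure. Any benefit already present in the earlier cases is subtracted along with the cohort gap.

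What is at stake is interpretation. The analysis is introduced as a way to explore simulator effects, directly after the admission of confounding. A reader could take a null result as no effect, or a positive one for theater time as harm, when simulator trainees were faster throughout. The contrast would also not yield a simulator effect freed of historical-cohort confounding: a constant cohort gap cancels only together with any constant part of the simulator effect, and a difference in trend between the cohorts stays in.

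**Working it through.** **Is there a pre-exposure period?** First exposure is in March. Follow-up is May to November (Study Design) or, on another reading of the Intervention section, the six months after the March weekend. Both begin after exposure. Prior operative experience enters Statistical Analysis only as a count of procedures. Comparators have no exposure date. On the described windows, the only within-trainee contrast is early versus late follow-up.

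**Algebra.** Let I and C be mean outcomes in the intervention and comparator cohorts, and let the effect in a period be I - C when the cohorts are otherwise alike.

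DiD = (I_late - I_early) - (C_late - C_early) = effect_late - effect_early

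Any cohort difference in trend is added to this. For theater time a benefit is negative. A constant benefit gives 0. With effect_early = 0, nothing is subtracted. With effect_early larger in size than effect_late, the result is positive.

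**Illustration.** The plan gives no figure for this analysis and no theater times, so these inputs are assumptions: theater time at case n is 60·n^(-a) minutes; early is the mean over cases 1-3 and late the mean over cases 6-8; the simulator is worth s extra cases of experience, so n becomes n + s.

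For a = 0.15 the comparator means are 54.99 (early) and 44.86 (late). With s = 2 throughout, the intervention means are 48.92 and 43.18:

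DiD = (43.18 - 48.92) - (44.86 - 54.99) = -5.74 + 10.13 = +4.39, that is +4.4 min.

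| Head start s (early, late) | Early effect, a = 0.15 | Late effect, a = 0.15 | DiD, a = 0.15 | DiD, a = 0.10 to 0.20 |
|---|---|---|---|---|
| 2, 2 | -6.1 | -1.7 | +4.4 | +3.0 to +5.7 |
| 4, 4 | -9.1 | -3.0 | +6.1 | +4.2 to +7.9 |
| 1, 4 | -3.8 | -3.0 | +0.8 | +0.4 to +1.3 |
| 0.5, 4 | -2.2 | -3.0 | -0.8 | -0.7 to -0.8 |
| 0, 4 | 0 | -3.0 | -3.0 | -2.2 to -3.6 |

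Simulator trainees are never slower in any row, yet the sign changes between rows. Only the last row, with no early effect, returns the late effect in full.

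**A second assumed curve.** With comparator theater time 45 + 15·exp(-month/tau), tau 2 to 4, and six months split into halves:

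- A head start worth 1 to 3 months gives a true mean effect of -1.7 to -4.1 min and a DiD of +1.2 to +4.7 min.
- A constant effect of -5 to -15 min gives a DiD of 0.
- An effect growing from -5 to -10 min has half-period means of -6.25 and -8.75, so the DiD is -8.75 + 6.25 = -2.5 min.

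The minutes depend on the assumed curves; the algebra does not.

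**The case against.** **The periods are inferred.** The article gives one sentence on this analysis, the timeline figure is not available, and a full protocol or analysis plan may define a pre-period. Statistical Analysis mentions data from before, or in the absence of, ongoing simulator use, and the Comparators section puts the newer rotation start in February, so a few weeks before the March weekend may exist. This stands as a limit on certainty. But no in-theater collection in those weeks is described, and the stated collection windows are all after exposure. The point is a conflict between the named analysis and those windows, not a missing detail.

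**The sign is not determined.** Someone might infer that a real benefit should be expected to show up as harm. The documents do not support that. Practice is repeated at least monthly, so the effect may build up; the last two rows of the table then have the correct sign. Reversal requires an early effect larger than the late one.

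**The analysis is minor.** It is exploratory and appears only in the Discussion. The mitigation wording there is attached to matching on training experience, not to this contrast. Statistical Analysis already plans direct comparisons between cohorts, and cumulative sum curves over follow-up are planned too. All of this stands and limits the weight of the point. It does not make the contrast interpretable.

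**Conclusion.** The point holds in a limited form. On the windows described, the difference-in-difference measures how the cohort difference changes during follow-up. It cannot estimate the simulator effect or clear it of historical-cohort confounding. It is zero for a constant benefit, attenuated for one growing from a non-zero start, and reversed if a head start fades. In the illustration it runs from +7.9 min (fixed head start of 4 cases, a = 0.20) to -3.6 min (head start growing from 0 to 4 cases, a = 0.20).

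These figures rest on an assumed curve, a starting theater time of about 60 min, and at least eight cases per trainee, none of which the documents give. The conclusion also rests on there being no pre-exposure period defined in material not shown.

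It would go too far to read this as a flaw in the main comparisons. The direct between-cohort analyses under Statistical Analysis do not subtract an early effect, although they remain open to confounding from the historical comparator. The change is worth making because it is cheap and alters what can be concluded.

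**What to change.** Replace the sentence in Strengths and Limitations along these lines: learning curves will be analysed with a mixed model, trainee as random effect, with cohort, case number and their interaction; the estimand is the cohort difference in level at matched case number (for example, averaged over the first cases); the cohort-by-case-number slope difference will be reported descriptively and not as the simulator effect; and the comparison remains open to confounding between calendar cohorts.

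Cost: a change of wording, slightly more modelling work, and giving up the claim of a difference-in-difference.

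A true difference-in-difference is optional. It would need in-theater outcomes for intervention cases before the March weekend, and for comparable weeks of training in comparators. That means further extraction: Primary End Points takes fluoroscopy counts and pin accuracy from imaging records and theater time from procedure reports, so logbooks alone would not suffice. For comparators whose rotations began in December, those weeks may fall before their February follow-up start. The window is short and likely to hold few cases, so any such analysis should be labelled exploratory.
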